## Discussion

AIH is known as a harmful disease with a high mortality which can easily progress to cirrhosis or liver failure. Prednisone plus azathioprine is considered the mainstay of therapy in the current recommendations for AIH therapy originate from this era. However, it does not provide good benefits for AIH patients because of its serious side effects. In this case, TCM has been popular used to treat AIH in China with good efficacy, low costs and small side effects. However, there is no rigorous and objective testing. What is more, Western medicine and TCM approaches have been used together to reach great effect worldwide [15]. Therefore, we conduct this study to explore whether the combination treatment of an empirical Chinese Herbal formula (SGJP Decoction) and steroids standard therapy could improve the clinical management of AIH.

This prospective study aims to explore the efficacy and safety of SGJP Decoction combined with steroid standard therapy on AIH. The achievement of this trial will provide evidence-based data for SGJP Decoction, which could provide good benefits for AIH patients. More over, the success of this study would represent justification and impetus for a large scale clinical study to further consolidate the evidence for the use of SGJP Decoction in AIH patients.

Our study also has several limitations that require consideration. Firstly, the case and control groups are not randomly assigned. However, we will use a new method of statistical analysis to make up for this shortage, the causal inference method, which has been used in previous randomized controlled trials [16]. In this method, propensity scores can balance the case and control group by limiting the confounding factors so that can help researchers to evaluate the interventions more accurately. Secondly, the sample size is still too small. However, the study produced critical data for sample size calculation of future study. And control of confounding variables, appropriate randomization, sufficient sample size and longer treatment period should be included in future study.

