## Background

Autoimmune hepatitis (AIH) is characterized by acute or chronic liver inflammation, which is considered to be associated with autoimmune response in liver cells. Previous studies [1] have proved that AIH can easily progress to cirrhosis or liver failure, and even some patients need for liver transplantation finally. It is reported that 40% of untreated severe AIH patients might die within 6 months, and those surviving commonly develop cirrhosis and subsequent complications of portal hypertension [2]. Moreover, it accounts for 2.6% of the transplantations in Europe [3] and 5.9% in the United States [4]. Due to this poor prognosis and the increasing detection rate, more and more studies focus on the management of AIH recently. It is well known that low dose prednisone plus azathioprine is the standard therapy for AIH, with alleviation of symptoms achieved in 60 to 80% of cases [5]. However, it must be noted that 50 to 86% of patients witness a recurrence of the disease after stopping medications, while 13% of patients stop the treatment too early due to the severity of the side effects and 9% of patients’ situation will deteriorate, even though they are administered medications according to guidelines [6]. Due to the high recurrence rate and the common side effects of corticosteroids, more and more AIH patients seek for traditional Chinese medicine (TCM) to manage their symptoms and reduce the side effects of corticosteroids in China.

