## Methods/design

### Study design

This is a prospective, non-randomized, controlled study. One-hundred and thirty two AIH patients visited in Guangdong provincial hospital of Chinese medicine at the first time will be enrolled and divided into two groups with a case: control ratio of approximately 1:1. While patients in the control group received the steroid standard therapy, patients in the case group are treated with combination treatment of SGJP decoction and the steroid therapy. Both of the treatment and follow-up period will be for 24 weeks. The details of the flow chart of this trial are shown in Fig. 1.

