### Patient population

A total of 132 AIH patients, who fulfill the screening criteria, is being enrolled and followed up between October 2015 and June 2017. According to the patients’ preference, the eligible AIH patients will be divided into two groups: the case group (to receive SGJP Decoction combined with low dose prednisone and azathioprine, *n* = 66) or a control group (to receive low dose prednisone and azathioprine, *n* = 66).

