## Conclusions

This prospective study will verify that SGJP Decoction could reduce steroid dosing and side effects of steroid. On one hand, it will give evidence data for SGJP on AIH so that it could be applied widely and bring more good benefits for AIH patients. On the other hand, the findings will provide a basis and a new direction for further confirmatory studies.

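### A propensity score balances only the recorded factors entered in it, so it cannot make good an allocation by patient preference, and the announced verification should become an adjusted association

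*Protocol article*

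**What the plan says.** The protocol article, Study design, states "This is a prospective, non-randomized, controlled study". Patient population gives the allocation mechanism: "According to the patients’ preference, the eligible AIH patients will be divided into two groups".

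The Discussion lists this as the first limitation, "Firstly, the case and control groups are not randomly assigned", and offers a remedy in the next sentence: "we will use a new method of statistical analysis to make up for this shortage, the causal inference method". The reason given is that "propensity scores can balance the case and control group by limiting the confounding factors". The text does not restrict this to measured factors and does not state an assumption of no unmeasured confounding. It supports the method by pointing to its use in earlier randomised trials.

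The Conclusions then announce: "This prospective study will verify that SGJP Decoction could reduce steroid dosing and side effects of steroid".

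The Background says what leads patients to the herbal treatment: "Due to the high recurrence rate and the common side effects of corticosteroids, more and more AIH patients seek for traditional Chinese medicine".

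**The concern.** The Discussion credits the propensity score with a property that belongs to randomisation. Randomisation balances recorded and unrecorded factors in expectation. A propensity score balances the covariates put into it, and other factors only so far as they are correlated with those covariates. Use of the method in randomised trials is no precedent here, because assignment in those trials is not confounded by preference.

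The problem is concrete in this study. The Background names recurrence and steroid side effects as reasons for seeking traditional medicine. The Inclusion criteria admit relapsed as well as newly diagnosed patients, so earlier experience of steroids will differ between patients. The primary outcome requires freedom from steroid-specific side effects as well as biochemical remission. A history of relapse or steroid intolerance can therefore influence both the choice of group and the endpoint. The direction of the resulting bias is not known in advance.

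At stake is how an adjusted result would be read. With the present wording, a favourable one would be presented as verification, although part of it could come from who chose the decoction.

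**Working it through.** **The plan's own figures.** Sample size and statistical methods gives 110 evaluable patients by expert agreement and 132 after 15% dropout. 110 / (1 − 0.15) = 129.4, rounded up to 130, which is within two patients of 132 (110 × 1.2 gives 132 exactly). The point does not depend on this difference. The figures are used only for the group sizes: 110 / 2 = 55 evaluable and 132 / 2 = 66 enrolled per group.

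**Assumed inputs (none is in the documents).** No treatment effect; 50% complete response in the control group; every recorded factor balanced by the propensity score; one unrecorded factor present in p1 = 60% of the case group and p0 = 30% of controls; the factor multiplies the chance of response by R.

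**Bias ratio** = (1 + p1(R − 1)) / (1 + p0(R − 1)).

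- R = 1.5: (1 + 0.6 × 0.5) / (1 + 0.3 × 0.5) = 1.30 / 1.15 = 1.130. The case group shows 50% × 1.130 = 56.5%.
- R = 2: (1 + 0.6) / (1 + 0.3) = 1.60 / 1.30 = 1.231. The case group shows 50% × 1.231 = 61.5%.

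**Chance of a false benefit.** This uses a pooled two-proportion z test at two-sided 0.05, counts only results that favour the case group, and enumerates the binomial outcomes exactly. The nominal rate without bias is 2.5%.

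| Factor effect R | 55 per group | 66 per group |
|---|---|---|
| 1.5 | 9.4% | 10.5% |
| 2 | 21.9% | 25.5% |

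A larger sample makes it worse, because the bias stays while the standard error shrinks.

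**A second set of assumptions.** These are two-sided error rates from the normal approximation, again with no treatment effect. The nominal rate is 5%.

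| Factor present, case vs control | Response with vs without factor | Spurious difference | Error, 55 to 66 per group |
|---|---|---|---|
| 60% vs 40% | 60% vs 40% | 4 points | 7.0% to 7.4% |
| 65% vs 35% | 60% vs 30% | 9 points | 15.7% to 17.9% |
| 70% vs 30% | 70% vs 30% | 16 points | 38.8% to 45.1% |

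**What a significant result needs at 55 per group.**

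- 39 vs 29 responders: difference 10/55 = 0.182; pooled proportion 68/110 = 0.618; standard error √(2 × 0.618 × 0.382 / 55) = 0.0927; z = 1.96, just significant. Risk ratio 39/29 = 1.34.
- 38 vs 27 responders: z = 2.13. Risk ratio 38/27 = 1.41.

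The E-value is RR + √(RR(RR − 1)). It gives 1.34 + √(1.34 × 0.34) = 2.0 and 1.41 + √(1.41 × 0.41) = 2.2. To account for such an estimate entirely, an unrecorded factor would need risk ratios of about 2.0 to 2.2 with both group and response. At a risk ratio of 1.3 the E-value is 1.92, but 1.3 would not be significant at this size when about half of the controls respond.

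**The case against.** The strongest reply is that the Discussion passage is a limitations paragraph. It calls non-random assignment a limitation, uses words of degree about what the score achieves, and leaves control of confounding and randomisation to a future study. The sample size text speaks of gathering information to plan a trial, the Discussion describes the aim as exploratory, and the Conclusions look to further confirmatory studies. This stands as a limit on severity: the article does not consistently claim full repair. It does not remove the point, because deferring control of confounding conflicts with saying that the shortage is made up for, and an exploratory aim conflicts with promising to verify.

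Four stronger readings are tempting, and the documents do not support them.

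- *A preference-related factor could produce the whole of a significant result.* In the 60% vs 30% scenarios the bias ratios are 1.13 and 1.23, below the 1.34 to 1.41 needed for significance. Chance must supply the rest, and a doubling of response is not a modest effect.
- *The plan treats an adjusted P below 0.05 as proof of causation.* No sentence says so. The Conclusions sentence concerns steroid dosing and side effects and is not tied to the propensity score, whereas the calculations above concern complete response.
- *The propensity model will hold only laboratory values.* The article lists no covariates, and the Inclusion criteria already separate first diagnosis from relapse, so some history is known.
- *The missing covariate list, matching method or sensitivity analysis is itself a defect.* An article commonly leaves these to the full protocol or analysis plan.

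A separate matter is that Sample size and statistical methods names only unadjusted tests while the Discussion promises adjustment. Those two places need reconciling, but the present point would remain after that.

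**Conclusion.** The point holds in a limited form. The Discussion attributes to the propensity score something it cannot do, and the Conclusions promise more than a preference-allocated comparison can deliver. No analysis plan can alter this, since a factor not collected cannot be adjusted for.

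The result is residual confounding of unknown size and direction. The rise in false benefit to between 9% and 22% rests entirely on assumed response rates, prevalences and factor strength, and on a bias that happens to favour the case group. It shows that the error rate can be materially inflated, not that it will be. The change is worth making because it affects what is collected at baseline and what may be concluded, and recruitment is still open according to Trial status.

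**What to change.** 1. At baseline, before treatment starts, record in both groups the number of earlier relapses and any earlier steroid side effects, if the form does not already do so, and enter them in the propensity model. Do not enter the stated reason for choosing or declining the decoction: it is defined by the group itself, would separate the groups and would destroy overlap. For patients already enrolled, flag any history obtained retrospectively, since recall may be coloured by treatment.
2. Report an E-value for the adjusted primary estimate and for its confidence limit nearer to no effect.
3. In the Discussion, replace the statement that the method makes up for the shortage with *reduce confounding by measured factors*. In the Conclusions, replace the promise to verify with *will estimate the association, adjusted for measured factors*.

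The cost is a few baseline questions, one extra line of analysis and a more modest stated conclusion. History collected late from enrolled patients will be weaker than history taken before treatment.

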## Conclusions

This prospective study will verify that SGJP Decoction could reduce steroid dosing and side effects of steroid. On one hand, it will give evidence data for SGJP on AIH so that it could be applied widely and bring more good benefits for AIH patients. On the other hand, the findings will provide a basis and a new direction for further confirmatory studies.

### Trial status

This trial is currently recruiting participants.

## Abbreviations

AASLD: American Association for the Study of Liver Diseases
AIH: Autoimmune hepatitis
AST: Serum aspartate aminotransferase
AZA: Azathioprine
GGT: g-glutamyl transpeptidase
PRED: Prednisone
SGJP: Shu-Gan-Jian-Pi
SGJPD: Shu-Gan-Jian-Pi Decoction
TBIL: Total bilirubin
TCM: Traditional Chinese medicine
ULN: Upper limit of normal
